#### **4.6.4. Archiving**

The patient identification lists as well as all documentation forms, consent forms and other important trial documents are stored at the respective trial centres for at least 15 years in accordance with Section 13 (10) GCP-V.

## **5. Ethical and regulatory aspects**

### **5.1. Independent ethics committees**

A favourable assessment of the study is obtained from the responsible ethics committee. Only then is the study started. In each additional trial centre, the study is only conducted after the responsible ethics committee involved has determined the suitability of the trial site and the qualifications of the investigators.

### **5.2. Ethical conduct of the clinical trial**

This protocol and any subsequent amendments to the protocol have been or will be drawn up in accordance with the Declaration of Helsinki as amended in October 1996 (48th General Assembly of the World Medical Association, Somerset West, Republic of South Africa).

#### **5.2.1. Legal provisions and guidelines taken into account**

The present study will be conducted in accordance with the published principles of the Good Clinical Practice (ICH-GCP) guideline and the applicable legal requirements (in particular the GCP regulation). These principles include ethics committee procedures, patient information and informed consent, protocol compliance, administrative documents, data collection and record keeping. To protect personal data, this study will be conducted in accordance with the DSGVO.

### **5.3. Information and consent of the test subjects**

A patient can only be included in the study if they have given their consent to this after being informed verbally and in writing by a doctor, therapist or documentary about the nature, significance and scope of the study in an appropriate and comprehensible manner. At the same time as giving their consent, they must have declared that they agree to the data being recorded as part of the study and to it being reviewed by the responsible supervisory or federal authority. It must be clear to them that they can withdraw their consent at any time without giving reasons and without suffering any disadvantages as a result.

The original written consent will be kept in the study folder of the trial centre. The patient will be given a copy of the written patient information and the declaration of consent.

Patient information and consent form are attached.

The patient information and consent form, all other documents received by participants and any recruitment advertisements are submitted to the responsible ethics committee for approval before use.

Public media, notices and flyers in ENT and maxillofacial clinics/practices, oncology centres and publications on the homepage of the participating clinics/practices will be used to draw attention to the study and publicise it (Appendix 10). The study will also be publicised via posters and flyers, which will also be sent to self-help groups. Patients in follow-up care who qualify for the study will be approached directly about the study by the attending physician. All patients who are potentially eligible as study participants and would like to take part in the study will be informed and educated about the study. Participation in the study is voluntary. The confidentiality of the data is always observed and guaranteed.

#### **5.4. Subject insurance**

This study is not a study subject to compulsory insurance within the meaning of the AMG, the MPG or the Radiation Protection or X-ray Ordinance. No special (commuting) accident insurance will be taken out.

#### **5.5. Data protection**

##### **5.5.1. Protection of personal data**

The principal investigator protects the right of patients to their personal data and ensures that it is handled responsibly. All persons who have patient contact within the scope of the study or who have access to disease data or other data are obliged to maintain confidentiality. Data is only passed on in pseudonymised form and published in aggregated form. This means that tracing back to individual persons is largely excluded. All study participants must ensure that documents with names (e.g. the signed consent forms and the patient identification list) are treated confidentially and kept protected from unauthorised access. Only the pseudonymised patient identification is stated on documentation forms and any other documents that are forwarded to study participants.

##### **5.5.2. Storage and disclosure of pseudonymised data**

As part of the information provided for the study, patients are informed that the data collected will be forwarded to the study centre of Clinic III, Haematology, Oncology and Palliative Medicine at the UMR. Patients are informed that, as part of the study, all data will be forwarded to the UMR study centre exclusively in pseudonymised form, stored there and used for scientific evaluations and publications. No personal data will be sent. Persons who do not consent to their data being passed on cannot take part in the study.

## **6. Statistical methods and determination of the sample size**

### **6.1. Statistical and analytical plan**

The drop-out rate is estimated to determine the primary outcome of phase A (feasibility).

The statistics of the primary and secondary outcomes (phase B) include: descriptive statistics, calculation of the mean individual differences and testing for zero; t-test for dependent samples/Wilcoxon/McNemar), distribution test for equality  $\chi^2$ -test; risk assessment or determination of association measures and testing for zero; correlation/regression and analysis of variance with repeated measures.

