|                      | 
 
• Transmission of individual training plans including exercise videos, exercise manual and small equipment to local therapists
 
• Local instruction of patients in the training programme and distribution of materials, exercise manual, individual training videos and training diary
 
• Implementation of the home training programme over 12 weeks, including documentation of the training (recording of the scope of training) and weekly call from the local therapist (questioning status quo, motivation, recording of adverse events)
 
• After completion of intervention: initial questionnaire to record motivation and questionnaire survey (EORTC QLQ-30, EORTC H&N35 and GSLT-PAQ) and performance diagnostics post analogue to diagnostics pre
 
• Follow-up examination after a further 12 weeks analogue pre/post
 
• Recording of the participants included in the study and the number of those who completed the 12-week training programme in full
 
• Recording/recording the reason for discontinuation
 
                                                                                                                                                                                                                                                                                                                                                                                                       |

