| Sample size   | N = 60 (oh which 25 Phase A)                                                                                                                                                                                                                                                                                                                                                                                                                                                                                                                                                                                                                                                                                                                                                                                                                                                                                                                                                                                                                                                                                                                                                                                                                                                                                                                                                                                                                                                                                                             |

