#### **4.6.3. Data analysis**

This study is a prospective longitudinal study. The data will be analysed by estimating the drop-out rate, descriptive statistics, correlation tests (correlation and regression analysis) and multifactorial methods for testing differences (e.g. analysis of variance with repeated measures). The data will be analysed in cooperation with the IBIMA of the UMR.

The evaluation with regard to phase I (feasibility) will take place after 25 patients have been included in the study. In addition, ad hoc analyses will be performed. In the case of rapid recruitment, this will be paused at 60 patients included in the study and, if necessary, continued depending on the results of the analyses.

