#### **6.1.3. Primary outcome**

This study consists of two phases.

Phase A (feasibility & quality of life, n = 25):

The hypothesis is tested that the proportion of patients completing the training intervention in the home-based setting over 12 weeks is  $\geq 70\%$ .

Phase B (quality of life, n = 35, total n = 60):

The hypothesis will be tested that the global QoL score (EORTC-QLQ-30) will increase significantly after a 12-week training intervention in the home-based setting.

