## **6.2. Determination of the sample size**

The case number calculation of phase I is based on the calculation that with  $n = 24$ , a 30% dropout rate can be estimated with an accuracy of  $\pm 18\%$  at a confidence level of  $1 - \alpha = .95$  (2-sided) (nQuery® Advisor 7.0 Statistical Solutions Ltd., Boston, MA, USA).

The sample size calculation for the trial (phase B) is based on the results of Felser et al. (28): global QoL pre:  $50.1 \pm 16.4$ ; post:  $58.3 \pm 16.2$ ;  $r = 0.618$  resulting in an effect size of 0.5755, which is detectable on a confidence level of  $1 - \alpha = .95$  (2-sided) with  $n = 42$  patients (nQuery® Advisor 7.0 Statistical Solutions Ltd., Boston, MA, USA). Assuming a 30% dropout rate based on our experience, a total of  $N = 60$  patients is required to be included in the study.

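### The primary feasibility outcome is tied to the 25 Phase A patients, and no text uses all 60 for it, although completion is recorded in all of them

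*Protocol*

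**What the plan says.** Protocol section 2.4 names two primary outcomes: the percentage completing the home training over 12 weeks (Phase A) and the change in global quality of life (Phase B).

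The places that set a sample for the first outcome are these:

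- Section 6.1: "The drop-out rate is estimated to determine the primary outcome of phase A (feasibility"). No number is given here.
- Section 6.1.3: "Phase A (feasibility & quality of life, n = 25"). Under this label it continues: "The hypothesis is tested that the proportion of patients completing the training intervention in the home-based setting over 12 weeks is" at least 70%.
- Section 4.6.3: "The evaluation with regard to phase I (feasibility) will take place after 25 patients have been included in the study".
- Section 6.2 plans the precision of the drop-out estimate on n = 24, giving ±18 points at 30% drop-out.
- Synopsis, sample size: "N = 60 (oh which 25 Phase A").

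For the second outcome, section 6.1.3 has "Phase B (quality of life, n = 35, total n = 60"), so the two phases are pooled for quality of life.

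Data collection is not split by phase. The synopsis has the study record how many participants were included and "the number of those who completed the 12-week training programme in full". Section 4.6 has a training diary kept for all patients and a reason recorded for each drop-out. Section 4.5 describes a single home programme, with individually chosen exercises, for everyone.

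The data analysis entry in the synopsis and section 4.6.3 also list estimation of the drop-out rate in general terms, without a number of patients.

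**The concern.** Where a sample size is given for the primary feasibility outcome, it is 25 (24 in the precision calculation). Phase B has quality of life as its only primary outcome. Section 6.1.3 writes out a total of 60 for quality of life and gives no such total for completion. Read as written, the feasibility answer and the test of the 70% hypothesis come from 25 patients, and the other 35 do not contribute, although the same information is collected on them under the same intervention.

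Two things are at stake. The first is precision: a primary outcome would be reported with a much wider interval than the trial's own data allow. The second is clarity about which result counts. If an all-patient drop-out rate is also produced under the general wording, there will be two completion proportions for one primary hypothesis, the first already circulated in the interim report at 25 patients (section 8.1.1), and the protocol does not say which one decides.

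**Working it through.** **Inputs**

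- Assumed drop-out 30%, that is 70% completion; two-sided 95% confidence; planning n = 24; stated accuracy ±18 points (section 6.2).
- Phase A n = 25; total n = 60 (section 6.1.3 and synopsis).

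**Step 1: reproduce the protocol's figure.** The normal-approximation half-width is 1.96 × √(p(1 − p)/n), with p(1 − p) = 0.30 × 0.70 = 0.21.

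- n = 24: 1.96 × √(0.21/24) = 0.183, or ±18.3 points. This rounds to the stated ±18.
- Conversely, a half-width of exactly 0.18 needs 1.96² × 0.21/0.18² = 24.9 patients.

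The stated accuracy is reproduced, and 25 patients deliver it.

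**Step 2: compare 25 with 60 patients.**

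| n | Calculation | 95% half-width |
|---|---|---|
| 25 | 1.96 × √(0.21/25) | ±18.0 points |
| 60 | 1.96 × √(0.21/60) | ±11.6 points |

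The ratio is √(25/60) = 0.645. The interval from 60 patients is 35% narrower; equivalently, the one from 25 is 55% wider (1/0.645 = 1.55). Under this formula the ratio is the same at any completion rate, because p(1 − p) cancels.

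**Step 3: check with exact intervals.** Clopper-Pearson half-widths for drop-out near 30% are ±18.7 points for 7/25, ±19.3 for 8/25 and ±12.2 for 18/60. The comparison does not depend on the approximation.

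**Step 4: what this means for the 70% hypothesis.** Section 6.1.3 names no test. Suppose, as an assumption, that the hypothesis counts as shown when the exact two-sided 95% lower limit is at least 70%.

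- With 25 patients, at least 23 must complete (23/25 = 92%).
- With 60 patients, at least 50 must complete (50/60 = 83%).
- At the protocol's planning rate neither sample would show it: 18/25 gives 51% to 88%, and 42/60 gives 57% to 81%. Both intervals include 70%.

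The larger sample therefore lowers the observed rate needed, but it does not change the conclusion if completion is about 70%.

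**The case against.** **The design is deliberate.** A feasibility phase was sized for about ±18 points, 25 patients give that, and an evaluation and an interim report are planned at that number. An early reading necessarily uses the earliest patients. This stands as a defence of the early evaluation. It does not justify ending the feasibility answer there: no continue-or-stop rule is attached to the 25-patient result, and the only pause in recruitment that section 4.6.3 mentions is at 60.

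**An all-patient estimate is not ruled out.** The general mentions of drop-out estimation carry no sample size, so they may cover all participants. This stands too. A reader might infer that the later 35 patients are expressly excluded from any completion estimate; the text does not say that. What it lacks is any link between an all-patient estimate and the primary outcome or the 70% hypothesis. The sample of 25 is fixed in the protocol itself, so this is not a detail merely left for a statistical analysis plan.

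**Early centres.** A reader might also infer that the first 25 patients represent the centres that opened first, and that the result is biased for the multicentre setting. Section 5.1 lets further centres start only after their own ethics review, so staggered starts are possible. The text available gives no activation dates and no accrual by centre, so neither the presence nor the direction of such a bias can be judged.

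**The pilot's completion rate.** It is tempting to show that 60 patients would establish feasibility where 25 would not, using the pilot's 83%: 21/25 gives 64% to 95%, and 50/60 gives 71% to 92%. That illustration is weak. The pilot had 12 patients, who trained under supervision in small groups (section 2.2). The contrast is also on the edge: 49/60 gives 69.6% to 90.5%, which includes 70%.

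**Conclusion.** The point holds as a matter of precision and of an undefined final result. The protocol ties a primary outcome to 25 patients when 60 will supply the same information, and it does not say that the larger set decides. At 30% drop-out the cost is a 95% half-width of 18.0 instead of 11.6 points. The relative loss does not depend on the assumed rate under the normal approximation, and exact intervals agree closely.

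This rests on three assumptions: that the sample attached to Phase A in section 6.1.3 is the sample for its hypothesis, which is the natural reading but not an explicit restriction; that about 60 patients are enrolled, while section 4.6.3 allows recruitment to continue beyond that; and that completion is recorded the same way throughout, as sections 4.5 and 4.6 describe. The documents do not support a claim that the early evaluation is wrong, that the 25-patient result is biased, or that the conclusion on the 70% hypothesis would change.

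**What to change.** In section 6.1.3, state that:

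1. the evaluation after 25 patients gives an interim estimate of completion, with its 95% confidence interval;
2. the final primary feasibility result is the proportion completing among all enrolled patients (planned 60), with its 95% confidence interval, and this result decides the 70% hypothesis;
3. completion in the first 25 and in the later patients is shown side by side, descriptively.

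Section 6.1 and the synopsis should be aligned with this wording. Naming the deciding result before the interim report is written avoids a choice between two completion rates afterwards.

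No new patients, data or procedures are needed. The cost is a written, reasoned amendment signed by all authors under section 9, with ethics approval where that section requires it. The final feasibility answer also comes later than the 25-patient report, which remains available as the early reading.

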|  | 
Nicotine and alcohol consumption
 
Disease-specific data: Diagnosis incl. stage, year of diagnosis, medical treatment(s)
 
Data on sports history
 
Data on the intervention: Adverse events, motivation, satisfaction with support and documentation, amount of training, possible reason for and time of drop-out
 
→ Estimation of the dropout rate
 
→ Descriptive statistics
 
Questionnaires (pre/post/follow up): Information on QoL (EORTC QLQ-30, EORTC H&N35), physical activity (GSLTPAQ), assessment of current fatigue (POMS-F) on the day of the performance assessment
 
→ Calculation of the mean individual differences and testing for zero; t-test for dependent samples/ Wilcoxon/ McNemar
 
→ Analysis of variance with repeated measures
 
Functional diagnostics (pre/post/follow up):
 
Inter-tooth distance at maximum mouth opening, range of motion (ROM) of the shoulder joints and cervical spine, flexibility of the trunk (stand and reach test), Short Physical Performance Battery (balance, walking speed, leg strength), 6-minute walk test (cardiovascular and pulmonary performance) incl. BORG and CR-10 scale (perception of exertion and pain on exertion), optional bioimpedance analysis (BIA)
 
→ Calculation of the mean individual differences and testing for zero; t-test for dependent samples/ Wilcoxon/ McNemar
 
→ Distribution test for equality <math>\chi^2</math> test; risk assessment or determination of association measures and testing for zero;
 
→ Analysis of variance with repeated measures
 
→ Correlation/regression analyses
 
The data is analysed in collaboration with IBIMA (Institute of Biostatistics and Informatics in Medicine)
 |

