### **2.4. Primary outcome**

Phase A (Feasibility)

Percentage of patients who complete the training intervention in a home-based setting over 12 weeks

Phase B (Quality of life)

Change in global QoL score (EORTC-QLQ-30) after a 12-week training intervention in a home-based setting

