## **4.2. Discussion of the study design**

Primarily, the short and medium-term effect of home training on the QoL of the patients is analysed. This means that the focus is on the intra-individual change in QoL between the time points pre (before the intervention), post (after the intervention) and follow-up. A control group is therefore not absolutely necessary.

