#### **4.6. Dokumentation**

The following questionnaires are used for the pre, post and follow-up examinations:

- Questionnaire for recording disease-specific data (Appendix 1)
- General questionnaire for the collection of personal data (only initial examination) (Appendix 2)
- EORTC-QLQ-30 and EORTC Module H&N 35: Recording of QoL (Appendix 3)
- Godin Leisure-Time Physical Activity Questionnaire (GSLTPAQ): Assessment of physical activity (Appendix 4)
- Final questionnaire: assessment of satisfaction with training programme and media/small equipment provided and supervision, current motivation of study participants with regard to continuation of the training programme (final examination only) (Appendix 5)

Various tests are used to objectively assess physical performance, functionality and body composition. These include:

- Profile of moods states fatigue scale (POMS-F): recording the current mood
- Measurement of the incisal edge difference (SKD): recording the mobility of the temporomandibular joint
- Range of motion (ROM) measurement of the cervical spine and shoulder joints using manual goniometers (objective measurements) and assessment of the extent of movement/restrictions to movement from the patient's and therapist's perspective (subjective information)
- Stand and reach test: assessment of the mobility of the back muscles
- SPPB: Test battery to assess balance ability, leg strength and walking speed
- 6-minute walking test incl. BORG and CR-10 scale: Assessment of aerobic endurance capacity, recording of the subjective feeling of exertion and subjective exertion pain
- Optional BIA: measurement of body composition

The total duration of the performance diagnostics is approximately 30 minutes. The results are documented in a protocol (Appendix 6).

The examinations listed are carried out both before (pre-test) and after the home-based intervention (post-test) as well as three months follow-up.

For all patients, the extent of training is documented in a TTB (Appendix 7). In the event of a drop-out, the reason for the cancellation is recorded.

The weekly telephone calls on the status quo (scope of training, motivation) are recorded in writing (Appendix 8).

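### The only three-visit model named, repeated-measures ANOVA, would in its classical form drop patients who miss follow-up; a mixed model on all observed visits is a cheap improvement, and the primary paired test is unaffected

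*Protocol*

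**What the plan says.** The protocol schedules three measurement points. Section 4.6 states: "The examinations listed are carried out both before (pre-test) and after the home-based intervention (post-test) as well as three months follow-up". Section 4.2 makes the course over these visits the main interest: "Primarily, the short and medium-term effect of home training on the QoL of the patients is analysed", and it adds that "the focus is on the intra-individual change in QoL between the time points pre (before the intervention), post (after the intervention) and follow-up".

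Two kinds of analysis of change are named:

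- A paired comparison. Section 6.1 lists "calculation of the mean individual differences and testing for zero; t-test for dependent samples/Wilcoxon/McNemar", and the synopsis lists the same for the questionnaires and the functional tests.
- A model for several visits. Section 6.1 lists "correlation/regression and analysis of variance with repeated measures". The synopsis lists "Analysis of variance with repeated measures" for both questionnaires and functional tests. Section 4.6.3 gives it only as an example: "multifactorial methods for testing differences (e.g. analysis of variance with repeated measures".

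The phase B primary outcome in section 2.4 is "Change in global QoL score (EORTC-QLQ-30) after a 12-week training intervention in a home-based setting", a pre-to-post change. Section 6.2 bases the sample size on the paired difference (effect size 0.5755, n = 42, N = 60 after 30% dropout). The protocol does not split this 30% between loss before the post-test and loss between post-test and follow-up. It does not say that incomplete patients will be excluded from any analysis, and it names no model that uses all available visits.

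**The concern.** Classical repeated-measures ANOVA works on patients with a value at every visit. A patient with pre and post values but no follow-up falls out of it, and the pre-post change already measured goes too. Three consequences may follow:

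- The ANOVA's short-term contrast is less precise than the data allow.
- It need not agree with the paired test of the same change, because the two would use different patients.
- If patients with lower QoL at post-test are the ones who do not return, the remaining patients have post-test values that are too high on average. The short-term gain then looks larger, and the fall from post-test to follow-up partly reflects regression to the mean.

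The last consequence touches the question whether the gain persists, which section 4.2 puts at the centre and which the medium-term secondary outcomes ask.

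**Working it through.** **Inputs from section 6.2:** pre 50.1 (SD 16.4), post 58.3 (SD 16.2), r = 0.618, two-sided 5% level, n = 42, N = 60, 30% dropout.

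**Assumptions, not in the documents:** 10, 20 or 30% of post-test completers miss follow-up. For the bias only: SD 16.3 at each visit, correlation 0.70 between post and follow-up, and log-odds of missing follow-up that rise by 0.05 or 0.08 per point of lower post-test QoL.

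**1. The plan's own figures.**
- SD of the difference = √(16.4² + 16.2² − 2 × 0.618 × 16.4 × 16.2) = 14.25.
- Effect size = 8.2 / 14.25 = 0.5755.
- Paired t-test with n = 42: power 95.4% (noncentral t).
- 42 / 0.70 = 60.

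All three stated figures are reproduced. The 30% allowance takes 60 exactly to 42 for the pre/post comparison, with nothing further set aside for follow-up.

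**2. Precision of the pre-post contrast.** The paired test on 42 patients has SE = 14.25 / √42 = 2.20.

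A mixed model with unstructured covariance also uses the 18 patients seen only at baseline. The slope of post on pre is b = 0.618 × 16.2 / 16.4 = 0.610, and the variance is 16.2² × (1 − 0.618²) / 42 + (1 − b)² × 16.4² / 60 = 3.86 + 0.68 = 4.54. The SE is 2.13.

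The ANOVA restricted to patients with all three visits has SE = 14.25 / √n:

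| Miss follow-up (assumed) | n in ANOVA | SE | vs paired test (2.20) | vs mixed model (2.13) | Power of this contrast |
|---|---|---|---|---|---|
| 10% | 38 | 2.31 | +5% | +8% | 93.2% |
| 20% | 34 | 2.44 | +11% | +15% | 90.3% |
| 30% | 29 | 2.65 | +20% | +24% | 84.9% |

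In simulated trials, where the number of completers varies, the last comparison with the mixed model is about 25% (SD 2.63 against 2.10).

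**3. Bias if loss depends on post-test QoL.** Let m be the amount by which the mean post-test score of the patients who return exceeds that of all 42. With equal SDs, their mean pre-test score is raised by 0.618 m and their mean follow-up score by 0.70 m. So:
- the pre-post contrast is biased by (1 − 0.618) m;
- the post-to-follow-up contrast is biased by (0.70 − 1) m;
- the pre-to-follow-up contrast is biased by (0.70 − 0.618) m.

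Finding m by numerical integration over a normal distribution gives:

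| Loss | m (log-odds 0.05 / 0.08) | Pre-post | Post to follow-up | Pre to follow-up |
|---|---|---|---|---|
| 10% | 1.25 / 1.81 | +0.5 / +0.7 | −0.4 / −0.5 | +0.1 / +0.1 |
| 20% | 2.41 / 3.39 | +0.9 / +1.3 | −0.7 / −1.0 | +0.2 / +0.3 |
| 30% | 3.53 / 4.91 | +1.3 / +1.9 | −1.1 / −1.5 | +0.3 / +0.4 |

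Simulations at trial size gave pre-post figures between about +0.4 and +2.1, with the mixed model within about 0.2 of the truth. If loss is unrelated to outcome, m = 0 and all three biases vanish.

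**The case against.** The strongest reply is that the plan already keeps these patients where it matters most. The paired test needs only the two visits compared. It is listed for primary and secondary outcomes and underlies the sample size, so missing follow-up visits leave the phase B primary comparison untouched. That stands. It does not reach the post-to-follow-up comparison, because a paired test there uses only returning patients and carries the same possible decline as the ANOVA.

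Second, the ANOVA is one item in a list, and an example in section 4.6.3. No section prescribes a complete-case set or says that the short-term effect will be read from the ANOVA, and an SAP may settle how missing visits are handled. That also stands. The point is therefore not that a missing-data rule is absent, but that the one three-visit model named suits the expected data poorly.

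Third, the loss rates and their link to outcome are assumed. If part of the 30% allowance was meant for follow-up, the further loss is smaller. In the supervised pilot described in section 2.2, 83% completed. The bias figures also assume that loss depends on an observed value, which is the setting that favours the mixed model.

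A reader might infer that the trial's three-visit outcomes rest on the ANOVA alone, that the plan is certain to discard patients, or that the primary result is biased. The protocol supports none of these. A reader might also infer that, within the ANOVA, short- and medium-term contrasts come from different patients. They do not: both use the same patients with all three visits. Different sets arise only between separate paired tests, or between a paired test and the ANOVA.

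**Conclusion.** The point holds in a limited form, as a cheap improvement and not as a fault in the primary analysis. The loss of precision in the ANOVA's pre-post contrast arises whenever follow-up visits are missed: 5 to 20% in SE against the paired test, or 8 to 25% against a mixed model that also uses baseline-only patients, for an assumed 10 to 30% loss among 42. Bias is conditional. It needs follow-up loss related to outcome, and under the assumed link to post-test QoL it is roughly +0.4 to +2 points on 8.2 for the pre-post contrast and −0.4 to −1.5 for post to follow-up. The second figure matters more for interpretation, because the paired tests do not remove it.

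**What to change.** In section 4.6.3, section 6.1 and the synopsis, for the continuous outcomes measured at pre, post and follow-up, replace repeated-measures ANOVA with a linear mixed model: visit as a fixed factor with three levels, unstructured within-patient covariance, and all available visits of all enrolled patients. Report the pre-post, pre-to-follow-up and post-to-follow-up contrasts from this model with 95% confidence intervals. State that the paired pre/post test remains the phase B primary analysis, so that it is clear which estimate of the short-term change counts.

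The cost is a change of wording. No further patients, visits or data are needed, and standard software fits the model. The downside is reliance on data being missing at random given the observed visits, which is a weaker assumption than the complete-case ANOVA needs. The model does not protect against loss that depends on unobserved follow-up values.
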